## Abstract

**Background:**

Although breast milk has numerous benefits for infants’ development, with greater effects in those born preterm (at < 37 gestational weeks), mothers of preterm infants have shorter breastfeeding duration than mothers of term infants. One of the explanations proposed is the difficulties in the transition from a Neonatal Intensive Care Unit (NICU) to the home environment. A person-centred proactive telephone support intervention after discharge from NICU is expected to promote mothers’ sense of trust in their own capacity and thereby facilitate breastfeeding.

**Methods/design:**

A multicentre randomized controlled trial has been designed to evaluate the effectiveness and cost-effectiveness of person-centred proactive telephone support on breastfeeding outcomes for mothers of preterm infants. Participating mothers will be randomized to either an intervention group or control group. In the intervention group person-centred proactive telephone support will be provided, in which the support team phones the mother daily for up to 14 days after hospital discharge. In the control group, mothers are offered a person-centred reactive support where mothers can phone the breastfeeding support team up to day 14 after hospital discharge. The intervention group will also be offered the same reactive telephone support as the control group. A stratified block randomization will be used; group allocation will be by high or low socioeconomic status and by NICU. Recruitment will be performed continuously until 1116 mothers (I: 558 C: 558) have been included. Primary outcome: proportion of mothers exclusively breastfeeding at eight weeks after discharge. Secondary outcomes: proportion of breastfeeding (exclusive, partial, none and method of feeding), mothers satisfaction with breastfeeding, attachment, stress and quality of life in mothers/partners at eight weeks after hospital discharge and at six months postnatal age. Data will be collected by researchers blind to group allocation for the primary outcome. A qualitative evaluation of experiences of receiving/providing the intervention will also be undertaken with mothers and staff.

**Discussion:**

This paper presents the rationale, study design and protocol for a RCT providing person-centred proactive telephone support to mothers of preterm infants. Furthermore, with a health economic evaluation, the cost-effectiveness of the intervention will be assessed.

**Trial registration:**

NCT01806480

## Background

In most industrialized countries breastfeeding rates are far from the World Health Organization’s (WHO) recommendation of exclusive breastfeeding, with no other fluids or solids, for 6 months after birth [1] and hence efforts have been made to increase breastfeeding rates. A systematic review of 52 trials from 21 countries has demonstrated that lay support and additional professional support were the only effective interventions prolonging breastfeeding [2]. Telephone support interventions to increase breastfeeding duration have shown promise [3]. However, it has been suggested that the reason why breastfeeding telephone support interventions sometimes fail is that care is reactive rather than proactive [3].

A qualitative meta-synthesis of women’s experiences shows the importance of providing person-centred care in supporting breastfeeding [4]. The synthesis, which is derived mostly from face-to-face interactions, suggests that authentic presence and a facilitative approach, which involve supportive care and a trusting relationship, are experienced as helpful for women who want to breastfeed. McCormack and colleagues [5,6] have defined person-centred care as a model of care, which includes components such as: building mutual trust and understanding; treating the person as an individual; respecting the rights of the person, sharing decision-making, providing holistic care and developing therapeutic relationships. Furthermore, the care provider should engage with and have a sympathetic presence with the person [6]. It is suggested that outcomes of effective person-centred care are increased satisfaction with care, involvement in care, and a feeling of well-being [6].

Breastfeeding has been shown to be highly beneficial for nutritional, immunological, and cognitive development. Investments in service and strategies to enhance and maintain breastfeeding frequency and exclusivity can be cost-effective and increase the quality of life in infants by reducing acute and chronic diseases [7,8].

Compared to term infants, preterm infants are immature in their development and cannot be fully breastfed immediately after birth. Instead, mothers and infants experience a transition period from tube feeding to breastfeeding, in which mothers cannot take full responsibility for their infants’ nutrition and survival in the same way as parents of healthy infants born at term can [24]. Compared to mothers of term infants, mothers of preterm infants spend longer being a mother in a public hospital environment, in which they may become dependent on the benevolence and support of the staff [25-27]. The transition from a medical setting to a home environment can be difficult for the mothers, because of unsolved grief, imprints of institutional authority and feelings of guilt and shame [24,28]. Improved support to families after discharge from the NICUs has hence been suggested as crucial for parental role attainment and to help families with the transition to the home environment [29-32].

This person-centered proactive telephone support intervention aims to increase exclusive breastfeeding rates, assess the cost-effectiveness of the intervention, improve maternal satisfaction, increase parental attachment, wellbeing and reduce parental stress.

## Methods/design

### Aim and hypotheses

This is a multi-centre randomized controlled trial (RCT), blinded for research team for primary outcome measurement. The primary aim of the RCT is to evaluate the effectiveness of proactive person-centred telephone support provided to breastfeeding mothers of preterm infants for up to 14 days after hospital discharge from NICUs on exclusive breastfeeding. We hypothesize that proactive (health service initiated) telephone support offered to breastfeeding (exclusive or partial) mothers of preterm infants after hospital discharge is more effective than reactive (mother initiated, and defined as usual care) telephone support at increasing the proportion of mothers who are exclusively breastfeeding 8 weeks after discharge.

The secondary aim is to evaluate the effectiveness and cost-effectiveness of proactive telephone support on breastfeeding (exclusive, partial, none and method of feeding), mothers satisfaction with breastfeeding, attachment, parental stress and quality of life in mothers/partners at 8 weeks after hospital discharge and at six months postnatal age. We hypothesize that breastfeeding, maternal satisfaction with breastfeeding and attachment, parental stress, and quality in life will be improved in mothers and partners who receive proactive telephone support. In addition, a qualitative evaluation will be performed, by interviewing mothers and staff on their experiences of receiving and delivering proactive person-centred telephone support respectively.

This intervention has been piloted by [name] and colleagues on a postnatal ward in Scotland [33,34]. The implementation, experiences, process evaluation and results from that pilot have provided this planned RCT with important knowledge, crucial for the design. For example, the pilot study reported a 0.23 effect size in breastfeeding 6–8 weeks and that the median telephone call time was 5 minutes.

### Definitions

For the purpose of this trial, we have used the following definitions. Breastfeeding refers to a mother providing any breast milk to her infant, regardless of method. Exclusive breastfeeding refers to only breast milk with no other fluids or solids except for medications and vitamins, given to the infant in the previous 24 hours. Partial breastfeeding refers to breast milk and infant formula, given to the infant in the previous 24 hours.

Person-centred care is defined as building mutual trust and understanding between caregiver and person; treating the person as an individual; respecting the rights of the person, sharing decision-making, providing holistic care and developing therapeutic relationships. The care provider should also engage with and have a sympathetic presence with the person.

### Study sample

The study setting will be four general or referral NICUs level IIIa or IIIb [35], geographically spread over Sweden. Eligible participants for randomization are mothers with preterm infants (< 37 gestational weeks), admitted to one of the four selected NICUs for at least 48 hours and who breastfeed or express breast milk. Exclusion criteria: serious maternal medical or psychiatric problems at discharge; language problems that cannot be resolved; the infant is transferred to another hospital/unit after discharge; infants that are terminally ill.

### Sample size calculation

A priori power analysis has been calculated to determine an adequate sample size for the study. This is a study of independent cases and controls with 1 control per case. Prior data indicate that the exclusive breastfeeding rate at two months of corrected age in preterm infants is 0.53. If the true exclusive breastfeeding rate for intervention mothers is 0.615 (effect size 0.085), we will need to study 531 intervention mothers and 531 control mothers to be able to reject the null hypothesis that the exclusive breastfeeding rates for intervention and control mothers are equal with a probability (power) of 0.8, using the Chi-square test. The Type I error probability associated with this test of the null hypothesis is 0.05. We estimate that the drop-out rate will be 5%, therefore requiring an additional 54 mothers. In total we need a sample size of at least 1116 mothers (I: 558, C: 558). The trial is also powered for the subgroup, low SES mothers. It is estimated that the study period will be 18 months.

### Recruitment of the breastfeeding support team

A breastfeeding support team (BST) will be set up in each of the four NICUs (7 staff members/each unit). In the selection of BST members, personal qualities (e.g. warm personality, organizational skills) and willingness to be part of the team are important. The selection will be conducted differently in the NICUs depending on the NICU’s organization, culture in constituting ‘groups’ and feasibility.

### Recruitment procedure for participants

The BST members at each NICU will inform eligible mothers and their partners, verbally and in writing, about the study, 1–2 weeks prior to the infant’s potential discharge. Mothers who consent to participate in the study will be randomly allocated immediately after hospital discharge (within 24 h) to one of two groups; intervention (I), or control group (C).

### Randomization process

Mothers who meet the inclusion criteria and who provide consent will be randomized to either the proactive (I) or reactive (C) telephone support group. Each mother will be assigned an identification code when they consent to participate, which will be used at randomization and on all questionnaires. The randomization is done by the BST immediately after discharge (within 24 h) by an automated and secure web-based system administrated independent of the research team. A stratified block randomization will be used, with blocks of 25 high SES and 25 low SES mothers at each participating NICU. The randomization takes place after the BST have collected baseline birth, feeding and socio-demographic data so that the BST or mothers will not be biased by knowing the group assignment. The mothers will be informed of their randomization group immediately following randomization by a telephone call or text message. The study outline is presented in Figure 1.

**Figure 1 F1:**
[figure not shown]
Flowchart on the progress of the study.

### Intervention

The intervention in this study is proactive telephone support initiated by the BST based at the NICU from which the infant is discharged. Daily phone calls from a member of the BST to the mother will be performed from day 1 until day 14 after discharge. In addition, the mother has the option to call someone in the BST during the same period (reactive telephone support). The telephone support will be conducted with a person-centered approach, as defined earlier and will aim to provide continuity of care. Thus, the mother is enabled to talk about whatever feels important to her and establish a trusting relationship with BST members.

### Control group

The control group will be offered the opportunity for person-centred reactive telephone support initiated by the mother who can phone the support team from day 1 after discharge until day 14 after discharge, 08.00-16.00 every day. Each NICU will set up a specific telephone number for their telephone support, and schedule BST members to be available. The same level of person-centeredness will be provided for the mothers in the control group (reactive) as mothers in the intervention group (proactive).

### Study protocol

The BST members at each site will be educated in a two-day course prior study start provided by the first and last author. The course includes theoretical sessions on becoming a mother in a NICU environment, person centered care and breastfeeding physiology. It also includes a practical session on telephone support (including in how to handle cases when triage to other pathways are needed), and a seminar on research methodology with focus on conducting a RCT. The BST members will receive in-depth information about the study and instructions to procedures for handling informed consent, protocols, log books, baseline questionnaire and telephone systems.

Each unit will keep a Log-book, in which the BST will record data on all infants admitted to the NICU, admission date, gestation week, eligibility for inclusion, date assessed for eligibility, reason for exclusion and whether mothers that decline participation have been asked to voluntarily answer some baseline characteristic questions (i.e. age, parity, gestational age, delivery and maternal educational level). Data on mothers/partners and infants participating in the trial (i.e. name, phone number, address, identification code, and infant’s date of birth) will be recorded in the Log-book prior to hospital discharge. In addition, if any mothers drop out of the trial between informed consent and hospital discharge, the reasons will be recorded. Established data protocols on demographics, infant health and breastfeeding are filled in by a BST member at inclusion and at discharge. All information collected prior hospital discharge, will be forwarded to the researcher in charge, together with data on date of discharge. After hospital discharge, randomization will generate the group allocation which will be entered in to the log book. Only the BST in each unit will know the allocated group for each mother. The identification code will be used to identify all distributed questionnaires and link data to each trial participant. Project coordination and data collection at eight weeks after discharge and six months of infant’s postnatal age will be performed by the first author blind to randomization for the primary outcome. University data protection and quality assurance procedures will be followed. For quality control of data entry, another member of the research team will do a random check of data entry quality in 10% of sample cases.

### Baseline socio-demographic and birth data collection

Data collection for participating mothers and partners include: educational level, parity, mode of delivery, ethnicity, and smoking habits. Data collection for participating infants include: gender, single or multiple birth, gestational age (GA) at birth, weight at birth, days on ventilator/ Continuous Positive Airway Pressure (CPAP), length of hospital stay, GA and weight at discharge, neonatal sequelae at discharge, breast milk (exclusive, partial, formula milk) and method (breastfeeding, bottle, cup) at discharge. Table 1 details the time points when baseline data will be collected.

**Table 1 T1:** Time schedule for obtaining data on characteristics

**Baseline data**	**All infants admitted at the NICU**	**Trial participants at enrolment**	**Trial participants at discharge**
Date of birth	•	•	
Sex (infant)	•	•	
Gestational age	•	•	
Age (mothers/partners)		•	
Parity		•	
Birth weight		•	
Way of delivery		•	
Single/multiple birth		•	
Educational level (mother)		•	
Ethnicity (mother/partner)		•	
Weight at discharge			•
Date of discharge			•
Days ‘on leave’ before discharge*			•
Infant’s health			•
Parent’s health			•

*In Sweden, parents are sometimes enabled to take their infants home (hours or days), although still admitted to the NICU.

### Primary outcome

Data on feeding status at eight weeks after discharge will be obtained through a telephone call in which mothers are asked if they give their infant breast milk (i.e. exclusive, partial, none), the method of feeding (i.e. breast, bottle, cup, tube) and infant’s weight. If the mothers have ceased breast milk feeding, they are asked at what time they ceased. The person who makes the phone call will be blinded for study group.

### Secondary outcomes

Table 2 details the time points when the following outcomes will be collected:

Parental stress in mothers and partners will be measured through the Swedish Parenthood Stress Questionnaire (SPSQ) [36], an adapted version of the Parental Stress Index [37]. It measures perceived stress in parenting in five dimensions (incompetence, role restriction, social isolation, spouse relationship and health problems) and has 34 items.

Quality of life in mothers and partners will be measured through the Short-Form Health Survey (SF-36) [38]. It measures self reported physical and mental health and has 36 items.

Attachment between the infant and the mother will be measured through the Maternal Postnatal Attachment Scale (MPAS) [39]. The scale comprises mothers’ emotional response to their infants and dimensions relating to mother-infant attachment and has 19 items.

Mothers satisfaction with breastfeeding will be measured through the Maternal Breastfeeding Evaluation Scale (MBFES) [40], which measures mothers’ satisfaction with breastfeeding and has 30 items.

Breastfeeding (i.e. exclusive, partial, none and method) and infant’s weight at six months of postnatal age will be measured through questions in the compiled questionnaire (instruments/scales presented above) sent to mothers.

**Table 2 T2:** Time schedule for outcome measurements

**Measures**	**Baseline at discharge questionnaire**	**8 weeks after discharge phone call**	**8 weeks after discharge questionnaire**	**6 months PNA questionnaire**
Breastfeeding (exclusive, partial, non, method)	•	•	•	•
Breastfeeding satisfaction, MBFES (mother)			•	•
Parental stress, SPSQ (mother/partner)			•	•
Attachment, MPAS (mother)			•	•
Quality of life, SF-36 (mother/partner)	•		•	•
Infant’s health (well-being, visits to health care facilities (mother/partner)			•	•
Experience of BST telephone support (mothers/partners)			•	•
Experiences of breastfeeding support (at NICU and Child Health Service) (mothers/partners)			•	•

### Qualitative outcomes

Eight focus groups (four with participants from the intervention group and four from the control group) with about 8 mothers in each group will be held after the final follow up data from the study has been collected at 6 months, to avoid potential interactions. There will be an option to volunteer for qualitative interview on the questionnaire sent to the mothers 8 weeks after hospital discharge. This enables gaining rich information from women with a maximum diversity sample (i.e. age, SES, parity) for the focus groups. The focus of the group will be on experiences of the received support. Mothers who volunteer but are not selected to participate in a focus group will be given the opportunity to submit their comments through the study Website: http://www.amningsstod.se

In addition, after the study has finished, focus groups will be held with 1) the feeding support team (e.g. experiences of providing care during the trial, the opportunities and challenges, views about the workload and working relationships between the BST and other health service staff) and 2) staff working in the NICU who are not in the feeding teams (e.g. workload and work-organization in the unit) for each NICU, in total 8 groups.

### Process evaluation for the study

To evaluate intervention fidelity for person-centered telephone support throughout the study and between intervention and control groups, phone-calls made by each BST member on randomly selected dates, in the beginning, middle and at the end of the study period, will be recorded if the mother consents to it. Recorded phone calls will be analyzed with a thematic coding-scheme. This procedure is important in order to: 1) monitor that support given is person-centered and regardless of group (I or C) and to assess any change in implementation over time (beginning, middle or end of the study period).

In addition, during the study period, members of the research team will observe BST meetings (not when specific mothers are discussed) and NICU staff meetings. Furthermore, interviews with NICU managers will be conducted at the end of the study, with the aim to detect possible major changes (e.g. in care/staff-infant ratio/environment) or problems that have occurred during the study period. Observations and notes will be recorded in a reflective diary, which will contribute to the qualitative data analysis.

### Data analysis

All members of the research team will be blind to the group allocation (I, C) throughout the study period and during analyses of primary outcome. Intention-to-treat will be used. This means that analyses will include all randomized mothers in the groups to which they were randomly assigned, regardless of their adherence with the entry criteria, regardless of the treatment they actually received, and regardless of subsequent withdrawal from treatment or deviation from the protocol. To study the differences between intervention group and control group on the primary outcome measure; the proportion of mothers who exclusively breastfeed 8 weeks after discharge, a two-sided Chi - square test will used. The level of significance; p-value is set at p <0.05 in all analyses. The specific statistical analysis used with each outcome variable will be determined by the distribution of the outcome variables. Subgroup analyses will be conducted on SES (low vs. high), parity (primipara vs. multipara), and on GA (very preterm vs. preterm).

Secondary outcomes will potentially be analyzed with a mixed effect model. A mixed effect modeling approach has several advantages when conducting a multicenter study with repeated measurements compared to a conventional analysis. For example, a mixed model, offers an insightful analysis and improved precision by taking into account the different centers in the analysis. In addition, a mixed model does not need complete data from all subjects. The result from a mixed model analysis presents a more accurate estimation of the intervention and standard errors [41].

All qualitative interview data from focus groups with mothers will be recorded, transcribed and analyzed; responses to open questions in the questionnaire will be transcribed. Transcripts will be read by two researchers to independently identify categories and key themes according to qualitative content analysis [42]. The categories and key themes will be discussed at research team meetings and a final version will be agreed. All data from focus groups with staff will be analyzed as with mothers. In addition these will be informed by data from BST meeting and ward observations recorded in a reflective diary. Qualitative data collection and analyses will be performed rigorously and supervised by experienced qualitative researchers.

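### The unstratified chi-square for the primary outcome is valid and keeps the stated power, but is slightly conservative because it ignores the SES and NICU strata used for randomisation

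*Protocol article*

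**What the plan says.** The Randomization process section of the protocol article states: "A stratified block randomization will be used, with blocks of 25 high SES and 25 low SES mothers at each participating NICU". The Study sample section names four NICUs, so there are 4 × 2 = 8 strata.

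For the primary outcome, exclusive breastfeeding eight weeks after discharge, the Data analysis section says that "a two-sided Chi - square test will used", and that the "p-value is set at p <0.05 in all analyses". It names no stratified or adjusted primary analysis. SES appears there only as a subgroup factor. Centre appears only in a mixed model that may be used for the secondary outcomes, and that model is credited with "improved precision by taking into account the different centers in the analysis".

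The Sample size calculation section uses the same unstratified test, "with a probability (power) of 0.8, using the Chi-square test", and adds: "The Type I error probability associated with this test of the null hypothesis is 0.05".

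The Background treats education as the best proxy for SES. It cites unpublished data in which 68% of mothers with higher education and 47% of those with less breastfed exclusively at two months.

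**The concern.** Stratified allocation balances the arms on SES and NICU, so differences between strata contribute almost nothing to the sampling variation of the treatment difference. The pooled chi-square does not use this. Its variance is the total variance, within strata plus between strata. If a stratification factor predicts the outcome, as SES does here, the standard error comes out too large. The p-value, and any interval built on the same variance, is then somewhat too cautious.

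What is at stake is efficiency: a little power and a slightly wider interval on the outcome for which the trial is sized. The remedy needs no extra data, because both factors must be known before a mother can be randomised.

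**Working it through.** **1. The plan's own figure.** Inputs from Sample size calculation: control rate 0.53, intervention rate 0.615 (difference 0.085), two-sided 5%, power 0.8, 1:1 allocation. The mean rate is (0.53 + 0.615)/2 = 0.5725. With the pooled-variance formula and no continuity correction:

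n = [1.960·√(2 × 0.5725 × 0.4275) + 0.842·√(0.53 × 0.47 + 0.615 × 0.385)]² / 0.085² = 530.6, so 531 per arm.

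This matches the protocol. Adding 5% gives 558 per arm and 1116 in total, as stated.

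**2. SES share that agrees with the protocol's rates.** The document does not give the share w of high-SES mothers. Solving 0.68w + 0.47(1 − w) = 0.53 gives w = 0.06/0.21 = 0.286.

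**3. Variance split under the null, SES only.**
- Total: 0.53 × 0.47 = 0.2491
- Between SES groups: 0.286 × 0.714 × 0.21² = 0.0090
- Within: 0.2491 − 0.0090 = 0.2401
- Ratio within/total: 0.964

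The true standard error is √0.964 = 0.982 of the one the chi-square uses, about 1.8% smaller. At 531 per arm the 95% half-width is 1.96·√(2 × 0.2491/531) = 6.0 percentage points unstratified and 1.96·√(2 × 0.2401/531) = 5.9 stratified.

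**4. True level.** 2·[1 − Φ(1.96/0.982)] = 0.0459, about 4.6%.

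**5. Power at 531 per arm, difference 0.085.**
- Standard error used by the chi-square: √(2 × 0.5725 × 0.4275/531) = 0.0304
- Within-stratum variance, averaged over the arms: (0.2401 + 0.2278)/2 = 0.2339. True standard error: √(2 × 0.2339/531) = 0.0297
- Plain: Φ[(0.085 − 1.96 × 0.0304)/0.0297] = 0.805
- Stratified: Φ[(0.085 − 1.96 × 0.0297)/0.0297] = 0.817

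**6. Equivalent sample size.** 531 × 0.964 = 512 per arm would give the same precision with stratification. On the recruited total, 1116 × 0.036 = 40 mothers.

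**7. Simulation.** 8 strata, permuted blocks of 25 (split 12/13), N = 1062, 100,000 null and 40,000 alternative runs, plain chi-square against Cochran-Mantel-Haenszel (CMH). The between-NICU SD, in percentage points, is an assumption.

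| High-SES share | NICU SD | Level, plain | Level, CMH | Power, plain | Power, CMH |
|---|---|---|---|---|---|
| 0.286 | 0 | 0.046 | 0.050 | 0.805 | 0.814 |
| 0.286 | 5 | 0.046 | 0.050 | 0.806 | 0.818 |
| 0.286 | 10 | 0.042 | 0.049 | 0.810 | 0.832 |
| 0.286 | 15 | 0.038 | 0.050 | 0.816 | 0.851 |
| 0.5 | 0 | 0.046 | 0.050 | 0.820 | 0.833 |
| 0.5 | 15 | 0.037 | 0.051 | 0.835 | 0.872 |

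The first row agrees with steps 4 and 5. At a share of 0.5 the overall control rate is 0.575, which departs from the stated 0.53; those rows show sensitivity only.

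**The case against.** The strongest reply is that the plan is coherent and the gain is small. The named test is the one that sized the trial, 531 per arm reproduces exactly, and 80% power is met. From SES alone, stratifying narrows the interval half-width from 6.0 to 5.9 points and adds about one point of power, which would rarely change a conclusion. All of this stands, and it limits the point to one of efficiency.

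Three stronger readings are tempting, and the document supports none of them.

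- *The 5% level is not held, so the test is invalid.* The true level lies below 5%, so false positives are not inflated.
- *The trial falls short of 80% power.* A reader who assumes equal SES halves and a within-stratum odds ratio of 1.42 will find about 76% against 77%. Those inputs imply a control rate of (0.68 + 0.47)/2 = 0.575 and a difference of about 0.079, whereas the protocol states 0.53 and 0.085. With the protocol's figures, plain power is about 0.805.
- *Centre effects are known to make the loss large.* The gains of 2 to 4 points in the table rest on an assumed NICU spread.

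It may also be said that the remark on centres concerns mixed models for repeated measurements, while the primary outcome is a single binary measure. That is fair: the remark shows that the authors know the benefit, but it does not contradict the primary test. Adjusted supplementary analyses might sit in an unseen analysis plan. The protocol does fix the primary test, however, and that choice is what is questioned here.

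**Conclusion.** The point holds as a modest loss of efficiency. The primary chi-square is valid and delivers the stated 80% power, but it leaves out prognostic factors on which allocation was balanced. Under the protocol's SES gradient and overall rate of 0.53, the true level is about 4.6% and about one point of power goes unused (about 0.805 against 0.815), worth roughly 40 of 1116 mothers.

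This rests on two assumptions: that the 68%/47% gradient at two months carries over to eight weeks after discharge, and that the high-SES share is 0.286. The share matters little: for shares from 0.286 to 0.7, SES alone gives an analytic level of 4.5% to 4.6%. The NICU contribution can only add to the loss, but its size is unknown. The change is worth making, though the trial does not fail without it.

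**What to change.** Name as the primary analysis a Cochran-Mantel-Haenszel test over the NICU × SES strata, reported with a stratified risk difference and its 95% confidence interval. An acceptable alternative is logistic regression with NICU and SES as covariates, reported as a standardised risk difference so that the effect stays on the scale used for sizing rather than becoming a conditional odds ratio. Keep the unadjusted chi-square as a sensitivity analysis.

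The cost is a change of wording. No new data are needed, and strata average 1062/8 ≈ 133 evaluable mothers, so sparse cells should not be an obstacle. The sample size can stay as it is. The primary test will no longer be identical to the one used for sizing, so a sentence should say that the calculation is slightly cautious for the stratified test. The change should be fixed before anyone sees outcome data by group, because a later switch would look data-driven.
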